## Abstract

Preterm infants are at risk for developing altered trajectories of cognitive, social, and linguistic competences compared to a term population. This is mainly due to medical and environmental factors, as they are exposed to an atypical auditory environment and simultaneously, long periods of early separation from their parents. The short-term effects of early vocal contact (EVC) on an infant’s early stability have been investigated. However, there is limited evidence of its impact on the infant’s autonomic nervous system maturation, as indexed by heart rate variability, and its long-term impact on infant neurodevelopment. Our multi-centric study aims to investigate the effects of EVC on a preterm infant’s physiology, neurobehaviour, and development. Eighty stable preterm infants, born at 25–32 weeks and 6 days gestational age, without specific abnormalities, will be enrolled and randomised to either an intervention or control group. The intervention group will receive EVC, where mothers will talk and sing to their infants for 10 min three times per week for 2 weeks. Mothers in the control group will be encouraged to spend the same amount of time next to the incubator and observe the infant’s behaviour through a standard cluster of indicators. Infants will be assessed at baseline; the end of the intervention; term equivalent age; and 3, 6, 12, and 24 months corrected age, with a battery of physiological, neurobehavioral, and developmental measures. Early interventions in the neonatal intensive care unit have demonstrated effects on the neurodevelopment of preterm infants, thereby lowering the negative long-term effects of an atypical auditory and interactional environment. Our proposed study will provide new insight into mother–infant early contact as a protective intervention against the sequelae of prematurity during this sensitive period of development. Early intervention, such as EVC, is intuitive and easy to implement in the daily care of preterm infants. However, its long-term effects on infant neurodevelopment and maternal sensitivity and stress are still unclear. Trial Registration: NCT04759573, retrospectively registered, 17 February 2021.

## 1. Background

Preterm birth rates are continuously increasing in most countries and over 500,000 infants are born prematurely every year [1]. Despite rapid advances in technology, the number of preterm infants with low gestational age (GA) at birth, who demonstrate short- and long-term sequelae of prematurity before reaching school age remains high [2]. Approximately 40% of low birth weight preterm infants experience a complex spectrum of unfavorable neurodevelopment outcomes [3] compared with their full-term peers. Thus, prematurity is of great concern for health policies, in both low and high-income countries [4,5]. The aforementioned impaired development of preterm infants is associated with medical factors and partly a consequence of their atypical early-life environment, including uncontrolled sensory inputs, pain stressors, and early maternal separation [6,7,8] during their hospitalisation in the neonatal intensive care unit (NICU). 

Developmental care practices aim to minimise the stress of the NICU environment through specific interventions, which may include control of external sensory stimuli [9] pain and stress management, and increased family involvement in the preterm infant’s care [10]. Health policies for guidelines in the NICU are still inhomogeneous, especially regarding parental presence in the NICU and family-centred care. Specific guidelines have recently been published with the support of an interdisciplinary group of experts, comprising paediatricians, parents, neonatologists, psychologists, and therapists [11]. These, hopefully, will be broadly adopted in NICUs in the forthcoming years.

### 1.1. Medical End Environmental Factors Lead the Preterm Infants’ Development

In addition to critical medical conditions, there is evidence that the NICU environment, to which preterm infants are exposed during the critical periods of brain maturation, can interfere with development. Early stressful experiences, particularly those related to an altered sensory exposure [12], painful procedures [7], and separation from primary caregivers [13] are considered among the most deleterious environmental factors affecting preterm infant’s development. The experience of this atypical environment during the sensitive and vulnerable period of brain growth may have negative cascading effects on their neuropsychological development [14].

The first year of life coincides with maximal brain growth, but is also the most vulnerable period in development. Preterm birth exposes infants to a severe mismatch with foetal brain development, which presents a significant challenge for a developing brain. The third trimester of gestation is a period of striking sequential brain changes [15]. Neurogenetic events occur across the cerebral compartments of the brain, including white matter tract growth, where the outgrowth of axons involved in pathway finding, guidance, and resting periods present a sensitive adaptation that can be affected by changes in the environment [16]. For early preterm infants, an important feature is the vulnerability of the thalamocortical pathways within the crossroads and sagittal strata. It is likely that this frenetic development of the brain and the diffuse subtle brain abnormalities found in preterm infants are influenced by environmental inputs [17]. 

In these phases, brain growth is activity-dependent, and the underlying mechanisms are regulated by early cortical synaptic activity. In animal models, researchers investigating the mechanisms of environmental enrichment or deprivation have reported a powerful effect of experience on brain development [18,19]. Therefore, the integrity of the brain processes depends upon the presence of the correct neural elements appearing at the appropriate developmental moments [20], in a delicate equilibrium between environmental stimulation and endogenous brain activity.

### 1.2. Atypical Auditory Environment in the NICU and Atypical Voice Treatment for Preterm Infants

The maturation of neuronal circuits during the third trimester of gestation is highly dependent on the intrinsic and extrinsic multisensory activity. The ability of foetuses and newborns to perceive the different sound levels in terms of energy (i.e., dBA) of the auditory stimulus [21], and sound pitches develops over time in utero and after full-term birth, due to the types and frequencies of sensory stimuli. For example, the tonotopic organisation of the cochlea continues maturing until early infancy and in cases of early exposure to loud background noise (e.g., preterm birth), it may fail to tune the hair cells of the cochlea, leading to frequency discrimination [22].

Instead of their mother’s womb, preterm infants spend the third trimester of gestation in a bright and unpredictable noisy place, the NICU. Stress during their stay in the NICU has been associated with more brain structural and functional alterations [23]. Conversely, protective actions aiming to avoid deleterious sensory stimuli and support a sensory-enriched environment during this period have demonstrated enhanced functional and structural brain development [24,25].

The auditory environment in the NICU is not always appropriate for sustaining the preterm infant’s auditory development; loud and unpredictable sounds from monitors, warnings associated with medical emergencies, hospital architectural characteristics (i.e., windows of the incubators, cabinet doors), and continuous background sounds (i.e., ventilators, CPAP) are common elements in everyday hospital soundscapes, often exceeding the recommended levels of sound pressure [24]. As such, acoustic criteria for the NICU have been proposed by Philbin and Evans [26] and clear recommendations for noise control in the NICU have been formulated [27].

The auditory development of preterm infants can encounter several problems in coordinating with the NICU’s soundscape. This is because the perception of a noise signal is not adult-like until late childhood and an immature auditory system can only perceive stimuli, even if salient (e.g., maternal voice) with an adequate signal-to-noise ratio [28]. Moreover, the predictability and organisation of background sounds affect attention, especially in infants and children, who require more repetitive and redundant auditory information than adults [29]. 

In the delicate balance between the inadequate soundscape of the NICU and a plastic and sensitive developing brain, whether and how the auditory experience of preterm infants in the NICU is controlled is crucial in early interventions.

Preterm infants at term-equivalent age treat voices atypically [30]. However, this discussion and interpretation are still debated. Bartha-Doering and colleagues [30] reported that full-term newborns demonstrate a significantly greater hemodynamic response to forward speech compared with backward speech within the left hemisphere, which is typically involved in language treatment. This suggests an altered development of the functional network underlying language acquisition in preterm infants, which is what further delays preterm infants from developing voice sensitivities in language areas. According to the authors this alteration in developing voice sensitivities in language areas is one of the potential reasons for further language delays in the preterm infants’ population. Adam-Darque and colleagues [31] interpreted their findings on additional cortical regions involved in voice processing and a late mismatch response to maternal voice in preterm versus term infants as potential positive signs for an earlier development of voice discrimination abilities in preterm infants, whose capacity to process voices may be enhanced due to an earlier airborne exposure to voices.

The amount of auditory experience adequate for perception and language development is unknown [32]. The debate surrounding early auditory enrichment with recorded stimulations is still open [33] and requires further investigation on the specific and distinctive tasks in preterm versus term voice perception and discrimination. This is for basic aspects such as forward and backward voices and early pitch (frequency), prosody (dynamic changes of pitch in time), melody, speech rhythm detection, and voice discrimination abilities.

### 1.3. Early Protective Interventions

A number of experimental studies have found that relation-based early interventions can impact infant development, mainly if they provide high-quality and ecologically pervasive actions [34], with the main effects lasting for the first two years of life [35]. Changes in sensory inputs and mother-driven environmental enrichment at this stage can affect brain development and stress regulation. Preterm birth carries severe risk factors for a dysfunctional mother-infant interaction cycle with the potential for developing lower maternal sensitivity and responsiveness and higher maternal control [36]. Both these forms of dysfunctional regulatory patterns show a lack of synchronicity, which is an essential element in the interactive regulation between developing attachment behaviour [37]. In the regulatory process of human attachment, maternal vocalisations to infants are “biologically relevant signals” [38] and affect brain development. The mother’s external regulation of the infant’s state during particular critical periods may represent the essential factor influencing the experience-dependent growth of brain areas, eliciting high levels of metabolic energy for the tuning of the brain cortical-subcortical circuits involved in processing socioemotional information [39].

Several studies investigated the effects of the live maternal voice—namely singing mothers supported by professionals—during music therapy interventions in the NICU, primarily suggesting it as an early music intervention in the frame of environmental enrichment and infant emotional development [40]. In these studies, the maternal singing, supported by instruments and by the music therapist, has been primary used to promote parent-infant interaction [41,42], to sustain preterm infants’ regulation and vital signs [43,44], and as a strategy to involve families in the early care in the NICU [45,46,47]. 

At this stage, early maternal care can affect an infant’s ability to react and positively adapt to stressful conditions: skin-to-skin contact [48], early vocal contact [49], maternal tactile stimulation [50], and active parental closeness.

### 1.4. EVC in the NICU Impacts Both the Auditory and Relational Environment

EVC actively involves parents in emotional and meaningful vocal contact with their preterm infants during hospitalisation in the NICU [49]. It sustains the preterm infant’s physiological stability, with a significant decrease in critical events (e.g., bradycardia, apnoea, and hypoxia) and increase in a calm awake state [51]. When preterm infants in the NICU are exposed to more adult voices, they show higher seven- and 18-month corrected age (CA) Bayley-III language and cognitive scores [52]. Low parental presence and the consequent decreased interaction and lower language exposure contribute to sensory deprivation experienced by infants in neonatal units, which impacts their brain structure and neurodevelopmental outcomes [12]. 

Filippa and colleagues illustrated the effects of live maternal vocalisations, singing and speaking, on the preterm infant’s behaviour [53] and reciprocally, the association between specific infant pro-social behaviour, such as smiling and opening eyes, and acoustic characteristics of the preterm infant-directed speech and singing [54]. The father’s vocal contact also impacts the preterm behavioural organisation and state in a manner similar to the mother’s voice, with calm awakening effects [55]. Changes in either parent’s vocal qualities are related to the preterm infant’s behaviour [56], indicating a reciprocal responsivity during early face-to-face interaction. 

The advances in intensive care have reduced neonatal mortality and severe outcomes such as cerebral palsy and sensory deficiencies. Conversely, there has been no concomitant reduction in consequential problems such as neurological disorders, subnormal cognitive function, language disorders, behavioural problems, learning disabilities, psychopathology (e.g., autism), and physical disability. The long-term developmental impairments of preterm babies are associated with perinatal, social, and relational risk factors. Further studies are needed to investigate the benefits of early healthcare and family-centred interventions for reducing the long-term impact of neonatal hospitalisation and minimising the negative impact due to invasive health interventions and stressful procedures. The lack of validated family-centred early interventions and the invasiveness of health technology assessment methods in preterm infants constitute the principal needs and challenges for further research. Moreover, no previous studies have evaluated the effect of EVC on a preterm infant’s autonomic maturation and at neurobehavioral and developmental levels.

### 1.5. Aims 

The proposed study aims to test the effects of EVC on infants born prematurely at 25–32 weeks and 6 days GA. The effects on newborns will be assessed at physiological (primary outcome), neurobehavioral, and developmental levels during the intervention, at term equivalent age, and at 6, 12, and 24 months CA. The effect of EVC on maternal stress at hospital discharge and on the mother’s presence in the NICU will also be assessed.

## 2. Hypothesis

We hypothesise that EVC can enrich the preterm infants’ sensory and interactional experience and that this mother-driven environmental enrichment impacts the infant’s physiology by enhancing cardiorespiratory maturation and autonomic regulation that persist during interventions and possibly heart rate variability (HRV). 

HRV is representative of the functional state of an infant’s autonomic nervous system (ANS). ANS maturation is accompanied by increasing HRV with a concomitant augmentation of parasympathetic activity. A preterm infant’s GA correlates with HRV; preterm infants demonstrate lower HRV parameters than term infants [57]. Early interventions aimed at involving parents in engaging with preterm infants have shown important effects on an infant’s HRV [58] and respiratory sinus arrhythmia [59], the two indices of autonomic regulation and maturation of the ANS. 

We also hypothesise that an interactive and relational-based enriched auditory environment can impact an infant’s neurobehavioral development, as evidenced by the General Movements score (for details, see Secondary Outcome Measures).

Specific interventions directed at improving early care in the NICU, such as the Newborn Developmental Care and Assessment Program [60], skin-to-skin care [61], and massage therapy [61,62], have shown significant effects on neurodevelopmental outcomes. Research suggests that early interventions aimed at reducing the sequelae of prematurity can have positive effects, especially in the short-term periods [63,64]. However, many interventions lack long-term assessments, particularly on the infants’ neural and behavioural development [65].

Thirdly, in a long-term prospective design, we will test if earlier and regular exposure to salient linguistic stimuli in interactive contexts will impact preterm infant development, particularly the cognitive and linguistic performance, at 6, 12, and 24 months CA. Adult language input is important for healthy language development and preterm infants are at risk for long-lasting language delays [66,67]. Thus, we expect to find a direct effect of the intervention on the aforementioned developmental domains.

Finally, we expect that EVC will reduce maternal stress in the NICU and increase maternal presence during hospitalisation by involving mothers in early interactions with their infants. Over the course of the past 50 years, several studies have confirmed that early mother-infant separation leads to adverse physiological and behavioural consequences that persist throughout life [68,69].

In general, we expect results that support the importance of EVC in the NICU and suggest that EVC may provide an effective, feasible, and easy-to-implement approach to improve outcomes in preterm infants.

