### 3.7. Sample Size and Power Analysis

The main outcome measures for the primary outcome will be the low-frequency (LF) and high-frequency (HF) power of the HRV measure. We expect the baseline measurement mean value (±standard deviation) of LF and HF power for preterm infants to be 31 ± 4.9 Hz and 15 ± 2.6 Hz, respectively [58]. We assume that the treatment in the experimental population is effective if the mean values of LF and HF power reach 25 ± 4.9 and 17 ± 2.4 Hz, respectively. 

With an alpha setting at 0.025 and beta setting at 0.80, it is necessary to enroll 29 patients per group. Assuming a 20% loss, we aim to enroll at least 80 patients total (40 per group).

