## 4. Measures

### 4.1. Baseline Measures

#### 4.1.1. Infant’s Measures

As a physiological assessment, electrocardiogram (ECG) recordings will be collected during a 20-min baseline period, in the absence of the mothers, at the same hour as that of the intervention. We will also use a qualitative assessment of general movements (GMs) to assess behaviour. A video of the baby’s general movements will be collected in the baseline period. The video coding will be performed on blinded videos by two independent researchers.

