## 5. Outcome Measures

### 5.1. Primary Outcome Measure

#### Physiological Level

During the interventions, time and frequency analysis of HRV will be applied to the following parameters: LFpower (power in the LF band), HFpower (power in the HF band), LFnu (normalised power in the LF band [LF power/(LFpower + HFpower)]); HFnu (normalised power in the HF band [HF power/(LFpower + HFpower)]); LF% (percentage power in the LF band [LF power/total power]), HF% (percentage power in the HF band [HF power/total power]), and LF/HF (ratio between LF power and HF power). The change from baseline will be calculated across the three conditions (i.e., singing, speaking, and control).

HRV will be measured through the acquisition of the ECG signal, via electrodes placed on the infant’s chest by routine medical devices. Subsequently, the ECG signal will automatically be recorded by the IxTrend Software (Ixellence GmbH, Wildau, Germany). Moreover, the heart rate (beats per minute), oxygen saturation (%), and all critical events (hypoxemia, oxygen saturation <80%; bradycardia, heart rate <80 bpm) will be acquired during the different conditions using the relevant medical apparatus. 

The physiological level is strictly dependent on the infant’s behavioural state (i.e., quiet, active, indeterminate, awake, or crying), which will be assessed offline from the video-recorded sessions by blinded coders, according to the Prechtl scale [8]. Measures of physiological parameters will be collected over the intervention period, as well as 20 min before and after the mother’s intervention.

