## 8. Statistical Analyses

### 8.1. Primary Outcome

The modulation of vagal activity will be tracked as a function of time during the interaction between the infants and mothers, by calculating the LF and HF power of the HRV and investigating respiratory sinus arrhythmia. The acquired autonomic signals (e.g., ECG, PPG, and breath signal) will be analysed to evaluate the differences between the physiological responses related to the different experimental groups. Standard analysis techniques that involve the extraction of parameters in the time and frequency domain will be applied in the first instance. 

Intra-group analysis (considering the control group and the intervention group separately) will be performed with the Friedman test by comparing the values of HRV parameters extracted from the three sessions (pre, yes and post). Post-hoc correction (Bonferroni method) will be applied. Inter-group analysis (between the control group and the intervention group) will be performed with the Kruskal–Wallis test by comparing HRV parameters of the first five-minute window of each session (pre, yes and post) between the two groups. Finally, innovative methods of analysis aimed at applying the chaos theory to physiological signals will be used to study the complexity of autonomic dynamics and the nonlinear coupling between the autonomic subsystems. These nonlinear analysis techniques will be applied both univariate (using a single signal, preferably HRV) and multivariate (e.g., considering HRV and pulse rate variability at the same time) domains.

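### The maturation part of the primary hypothesis has no matching test: Section 8.1 compares raw values around a session, although Section 5.1 defines the outcome as change from baseline

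*Protocol article*

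**What the plan says.** **Hypothesis.** The Abstract and the end of Section 1.4 present autonomic maturation as the gap in the evidence. Section 2 hypothesises an effect on "physiology by enhancing cardiorespiratory maturation and autonomic regulation that persist during interventions and possibly heart rate variability (HRV" and explains the link to HRV: "ANS maturation is accompanied by increasing HRV with a concomitant augmentation of parasympathetic activity".

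**Recordings.** Under baseline measures, Section 4.1.1 states that "electrocardiogram (ECG) recordings will be collected during a 20-min baseline period, in the absence of the mothers". Section 5.1 adds: "Measures of physiological parameters will be collected over the intervention period, as well as 20 min before and after the mother’s intervention".

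**Outcome definition.** Section 5.1: "The change from baseline will be calculated across the three conditions (i.e., singing, speaking, and control".

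**Analysis.** Section 8.1 opens with "The modulation of vagal activity will be tracked as a function of time during the interaction between the infants and mothers". Within each arm, a Friedman test works by "comparing the values of HRV parameters extracted from the three sessions (pre, yes and post". Between arms, a Kruskal–Wallis test compares the first five minutes of each of those three periods. Nonlinear analyses of the same signals follow.

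**Sample size.** Section 3.7 gives baseline means and SDs of 31 ± 4.9 (LF) and 15 ± 2.6 (HF). Its targets under treatment, 25 ± 4.9 for LF and 17 ± 2.4 for HF, are introduced with the words "We assume that the treatment in the experimental population is effective if the mean values of LF and HF power reach".

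**The concern.** A response to a voice and a change in autonomic maturation are different quantities. The first shows as a shift in HRV while the mother speaks or sings, and it may be gone within the hour. The second should show at rest, after the course, as a difference between infants who had EVC and infants of the same age who did not.

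The hypothesis claims both, but the stated tests are built around the session. A significant result from Section 8.1 could therefore be reported as maturation when it shows only a transient response. A true resting effect could also go untested, although the recordings needed to look for it are already planned.

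The outcome definition and the analysis also disagree. Section 5.1 promises change from baseline across three conditions (singing, speaking, control). Section 8.1 analyses raw values in three periods and two arms.

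**Working it through.** **1. The plan's own sample size.** Inputs from Section 3.7: alpha 0.025, taken as two-sided (sidedness is not stated); the stated 0.80 read as power; HF difference 17 − 15 = 2; LF difference 31 − 25 = 6. Formula: n per group = 2(z₁₋α/₂ + z_power)² × SD² / difference².

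- z values: 2.241 + 0.842 = 3.083; squared, 9.505.
- HF variance: (2.6² + 2.4²)/2 = 6.26. n = 2 × 9.505 × 6.26 / 4 = 29.75, so 30.
- LF: n = 2 × 9.505 × 24.01 / 36 = 12.7, so 13.
- Stated: 29. HF governs. With SD 2.4 and the t distribution n is 28.7, so 29. The figure reproduces.
- Dropout: 29/0.8 = 36.25, so 37 per group. The planned 40 covers this.

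The calculation is for two groups, so the baseline mean stands in for the control mean. That is where the wording of Section 3.7 slips: it describes treated versus baseline, while the number is for EVC versus control.

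**2. Hypothesis, outcome and test side by side.**

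| Target | Recording available | Test stated in 8.1 |
|---|---|---|
| Regulation during sessions (Section 2) | Before, during, after session (5.1) | Friedman within arm; Kruskal–Wallis between arms |
| Change from baseline (5.1) | Baseline ECG (4.1.1) | None |
| Maturation over the course (Section 2) | Baseline ECG; 20-minute pre-session recordings | None assigned |

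The Friedman tests are within-arm and so are not randomised comparisons. The Kruskal–Wallis test is randomised but has no baseline term.

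**3. Can the pre-session window serve as the maturation test?** There are 3 × 2 = 6 sessions. Section 8.1 does not say which are analysed or how they are combined. Before session 1 no infant has been exposed, so that window cannot show an effect. Before session 6 it could show carry-over from five earlier sessions. As written, the window is not a defined maturation test.

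**4. What baseline adjustment would do.** The documents give no correlation r between baseline and later HRV, so r is an assumption here. Relative to raw values, variance is multiplied by 1 − r² with adjustment and by 2(1 − r) with a simple change score.

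| Assumed r | Adjusted | Change score |
|---|---|---|
| 0.3 | 0.91 | 1.40 |
| 0.5 | 0.75 | 1.00 |
| 0.7 | 0.51 | 0.60 |

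Adjustment is the more precise of the two at each value shown, and it honours the baseline in Section 5.1.

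**5. Power for a maturation contrast.** It cannot be computed, because the documents give neither a maturation effect nor a within-infant correlation.

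**The case against.** **The session tests answer a stated question.** Section 2 also names regulation during interventions, and Section 5.1 sets the measurement during the interventions. This stands. It would be wrong to say that the trial does not address its primary hypothesis; it addresses one part.

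**The baseline is not ignored.** A reader might infer that the baseline ECG is collected and used nowhere. The text does not support that, because Section 5.1 speaks of change from baseline. That baseline could be the ECG of Section 4.1.1 or the recording before each session, and the article does not say. Under the second reading the change is by construction a within-session change, and maturation still lacks a test.

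**The pre-session comparison is not purely acute.** This is correct, and in later sessions it could reveal carry-over. It would need a named session to do so.

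**Power.** Since Section 2 says HRV rises with maturation, a reader might infer that controls will drift towards the target and the trial will lose power. That follows only if the EVC mean is held at 17 while controls rise. If EVC adds 2 to whatever controls reach, the difference stays at 2 and nothing is lost. The documents give no drift, and concurrent controls deal with maturation in the comparison itself. LF has about 99% power at 29 per group (normal approximation), so a loss worked out for HF alone would not be the trial's power.

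**Details may sit elsewhere.** Figure 1 is not shown and an analysis plan may exist. Extra ECG time points or covariates would be ordinary detail for those places. But the article itself fixes the primary tests, and they do not match its own outcome definition.

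**Conclusion.** The point holds in a limited form. The primary hypothesis has a maturation part and a regulation part. Section 8.1 tests the second and assigns no test to the first, and it departs from the change from baseline defined in Section 5.1. The consequence concerns interpretation: a positive Section 8.1 result would not by itself support a claim of maturation.

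No numerical size can be attached, and the stated sample size reproduces to within one infant per group. The conclusion assumes that Section 8.1 lists the primary tests in full and that Figure 1 contains no analysis that overrides them. The wording of Section 3.7 is a lesser matter of clarity.

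**What to change.** 1. Reconcile Sections 5.1 and 8.1, and state which recording is the baseline.
2. Add one prespecified between-arm comparison of resting HRV, taken from the 20-minute recording before the last session and adjusted for baseline HRV and the randomisation strata (gestational age and gender). State whether the mother is absent for that recording, as she is at baseline, so that the two are comparable.
3. Let only this comparison support a maturation claim. Report the during-session contrast as acute response.
4. State which of the two is confirmatory.
5. In Section 3.7, word the planned difference as EVC versus control at the same time point.

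The cost is some rewording and one extra model on recordings already planned. The real price is that the investigators must rank the two questions, and the one ranked second can no longer carry the main claim.
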